#### Secondary outcomes

Secondary outcomes include modifications of unhealthy lifestyles at 3, 9, and 12 months, and modifications of specific lifestyles (also including smoking, alcohol consumption, physical activity, diet, and BMI), sleep quality, drug intake adherence, smoking/drinking quitting, mental health outcomes, cognitive function, self-efficacy, implicit health attitudes, social support, frailty, and clinical outcomes at baseline, 3, 6, 9 and 12 months, with details as follows:

##### Sleep quality

Sleep quality will be measured with the Pittsburgh Sleep Quality Index (PSQI) [47].

##### Drug intake adherence

Drug intake adherence will be monitored by a self-designed scale to ask about the time of the most recent missed dose and medication-related behaviors, with reference to Medication Adherence Rating Scale (MARS) [48, 49].

##### Smoking/Drinking carving and quitting

Smoking/Drinking craving will be measured with the Visual Analogue Scale (VAS) and the Penn Alcohol Craving Scale (for smoking, with replacement of “alcohol” by “smoking”) [50]. Self-reported smoking or alcohol consumption uses the past seven days as reference period.

##### Mental health outcomes

Anxiety will be evaluated with the 7-item scale for General Anxiety Disorder (GAD-7) [51], and depression will be evaluated with the Patient Health Questionnaire Depression Module (PHQ-9) [52].

##### Cognitive function

Cognitive function will be measured with the Montreal Cognitive Assessment, Basic Version (MoCA-B) [53].

##### Self-efficacy

Self-efficacy will be measured using the General Self-Efficacy Scale (GSES) [54].

##### Implicit health attitudes

Implicit health attitudes will be measured according to the lay theories of healthy behavior intentions scale [55].

##### Social support

The modified Multidimensional Scale of Perceived Social Support (MSPSS) will be used to assess social support [56].

##### Frailty

Frailty will be assessed with the Phenotype of Frailty scale [57].

##### Clinical outcomes

Development of clinical outcomes related to lifestyles including general obesity, central obesity, hypertension, diabetes mellitus, dyslipidemia, sarcopenia, arteriosclerosis, osteoporosis, and fatty liver, will be compared with past medical history supplemented by physical examination and laboratory test indicators. Venous blood samples, collected after overnight fasting (at least 8 h), will be used for clinical laboratory testing, including routine blood tests, fasting blood glucose, lipid levels and hepatic function. If local clinical centers are not equipped with relevant testing devices, uniform devices will be provided and doctors and nurses will be trained to operate these devices, including bone mineral density densitometers (OSTEOKJ3000) among others. All procedures for clinical examinations will be in line with the standard operating procedures (SOPs) of the CMEC as documented elsewhere [33].

##### Metagenomics and metabolome

Gut microbes and their metabolites related to lifestyles will be detected using metagenomics and metabolomics. Respondents will be asked to collect 5-10 g of their own mid-morning stool on days of onsite assessments using a fecal collection cup issued in advance, that is then handed over to the field staff. After handover, it will be immediately checked and tested for quality, labeled, refrigerated in a 5L ice box and transported to a -80 °C refrigerator for temporary storage on the same day. The stool will be delivered to a Third-Party Medical Laboratory for multi-omics analysis. The procedure of sample collection and storage follows the SOPs of the CMEC as documented previously [33].

### Timeline of data collection

Participants who meet the inclusion criteria will undergo baseline data collection given informed consent. Communities will only be randomized after this baseline data collection, with corresponding allocation of participants to experimental or control group. Demographic characteristics and medical records data will respectively be surveyed and extracted at baseline. Primary outcome and secondary outcomes assessed with questionnaires and scales will be collected at five measurement points: baseline, 3 months after baseline, primary end-point. That is end of instructed intervention period (6-month follow-up), 9-month follow-up, and 12-month follow-up. Laboratory data will be collected at four time points: baseline, 3 months, primary end-point (6-month), and 12-month follow-up (Fig. 3).

**Fig. 3 Fig3:**
[figure not shown]
SPIRIT flow diagram for the schedule of enrolment, interventions, and assessments. FFQ, Food Frequency Questionnaire; IPAQ, short version of the International Physical Activity Questionnaire; PSQI, Pittsburgh Sleep Quality Index; GAD-7, 7-item scale for General Anxiety Disorder; PHQ-9, patient health questionnaire depression module; mGSES, modified General Self-Efficacy Scale; MoCA-B, Montreal Cognitive Assessment, Basic Version; mMSPSS, modified Multidimensional Scale of Perceived Social Support; SPPB: Short Physical Performance Battery; PWV, pulse wave velocity; QCT: Quantitative Computed Tomography; BMD: bone mineral density; CTA: computed tomography angiography. ^a^Blinding of participants, assessors, and statisticians. ^b^Body circumference included neck, waist, belly, hip, arm and leg circumference. ^c^SPPB included feet together test, semi-tandem stand test, tandem stand test, 4-m walk test, and five times sit-to-stand test. ^d^Color doppler ultrasonography included abdominal, carotid and cardiac ultrasonography. ^e^Blood tests include total white blood cell count (WBC), red blood cells (RBC), haemoglobin (HGB), platelets (PLT), lymphocytes, monocytes, neutrophils, eosinophils, fasting blood glucose fasting blood glucose (FBG), triglycerides (TG), cholesterol (CHOL), high-density lipoprotein cholesterol (HDL-CH) and low-density lipoprotein cholesterol (LDL-CH), total protein (TP), albumin, globulin, alanine transaminase (ALT), aspartate amino transferase (AST), gamma-glutamyl transpeptidase (GGT), Creatinine (Cr), urea, uric acid (UA) and C-reactive protein (CRP). ^f^Including metagenomics and metabolomics. X The item will be surveyed implemented or on relevant time point.

The item will be implemented in the relevant time period.

### Data analysis

Data analyses will be performed using R version 4.2.1 for Windows. All data will be securely stored in an electronic database and accessible only to researchers who meet the criteria as provided in the research ethics approval document.

Descriptive statistics will be provided for the baseline sample. Categorical variables will be summarized in terms of frequencies and percentage, in total and by intervention group. Continues variables will be summarized as mean ± standard or median (interquartile range) in total and by intervention group.

All main analyses will be performed on intention to treat (ITT) basis. The primary outcome will be analyzed with mixed effects log-linear Poisson regression of any reduction of unhealthy lifestyles at six months (favorable outcome vs not) on intervention group as randomized at baseline [58]. In addition, the model will include a random intercept for subject nested in village and a fixed effect for town (as number of clusters not sufficient for variance estimation in the latter case). Treatment effect at six months (immediately after intervention) will be provided as relative risk ratio [59]. As regards secondary outcomes, reduction of unhealthy lifestyles (favorable outcome vs. not) at all timepoints will be simultaneously analyzed with longitudinal mixed effects log-linear Poisson regression on timepoint, and an interaction term of timepoint and intervention group, with random intercepts for subject nested in village and fixed effect for town as specified for the primary outcome. Other binary outcomes including smoking/drinking quitting, drug intake adherence, frailty will be analyzed in the same fashion. For continuous outcomes including sleep quality, smoking/drinking carving, mental health outcomes, cognitive function, self-efficacy, implicit health attitude, social support, longitudinal analysis of covariance (ANCOVA) models with time and time-group interaction will be estimated, adjusted for the respective outcome at baseline and featuring random intercepts for subject nested in village as well as a fixed effect for town [60]. Estimates of differences in changes in lifestyles between groups at 3, 6, 9, and 12 months will be analyzed post hoc using Wald-tests.

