### Sample size

The primary outcome is the improvement of modifiable unhealthy lifestyles, with a reduction by at least one unhealthy lifestyle at 6 months considered a favorable outcome (coded 1) and any other outcome unfavorable (coded 0). According to a previous study, the prevalence of at least one unhealthy lifestyle in Chinese community residents is 89.6% [2, 37]. According to an analysis of the previous two survey waves of the CMEC, it is expected that 2 percent of the control group participants will achieve a favorable outcome. We assume that a 10% percent increase of participants with favorable outcome in the intervention group (to 12% in total) constitutes a minimally important difference.

To achieve a power *of* 0.80 to obtain a statistically significant signal at α <  = 0.05 for p_1_ = 0.02 vs. p_2_ = 0.12 with a chi-squared test of independence, the sample size is estimated as 204 (102 per group). To account for participant attrition of estimated 20%, recruitment target is 128 participants per group, with a total sample of 256 participants for assessment and evaluation.

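### The six-month primary model carries a redundant subject intercept and a Poisson variance unsuited to 0/1 data; its test is unnamed, and under a Wald test power is about 65%, not 80%

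*Protocol article*

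**What the plan says.** All references are to the protocol article.

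- **Outcome.** Under Sample size and Primary outcomes, each participant is scored once at six months: favourable (1) if at least one unhealthy lifestyle has gone, otherwise 0.
- **Primary model.** Data analysis states: "The primary outcome will be analyzed with mixed effects log-linear Poisson regression of any reduction of unhealthy lifestyles at six months". It continues: "In addition, the model will include a random intercept for subject nested in village and a fixed effect for town". The effect is reported as a relative risk. The model covering all timepoints is described separately, as a secondary analysis.
- **Other binary outcomes.** "Other binary outcomes including smoking/drinking quitting, drug intake adherence, frailty will be analyzed in the same fashion".
- **Planning.** The sample size rests on these statements: "it is expected that 2 percent of the control group participants will achieve a favorable outcome"; and an "increase of participants with favorable outcome in the intervention group (to 12% in total) constitutes a minimally important difference". The calculation is made "with a chi-squared test of independence", giving 102 evaluable per group, raised to 128 for 20% attrition.
- **Inference.** No test is named for the primary treatment effect. Wald tests are named for post hoc group differences at 3, 6, 9 and 12 months and for subgroup interactions. Under Missing values, all main analyses use multiple imputation with 100 sets.

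**The concern.** Three features of the stated analysis do not fit the data it will meet.

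1. A subject random intercept models correlation between repeated values in the same person. The primary model has none, so the term becomes an observation-level effect. It can only add variance to a Poisson model, whereas 0/1 data already vary less than Poisson: p(1−p) against p.
2. Unless a robust variance is used, standard errors take the Poisson variance p. The overstatement grows with prevalence, so it matters most for the secondary binary outcomes.
3. Sizing and analysis use different methods. A chi-squared test compares proportions; the analysis estimates a log risk ratio. With about 2 expected control events these can behave very differently, and the risk ratio may not exist.

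At stake are the power of the primary comparison, whether it returns an estimate at all, and the width of the intervals for secondary outcomes.

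**Working it through.** **Inputs from Sample size and Randomization:** control rate 0.02, intervention rate 0.12 (risk ratio 6), α 0.05 (two-sided assumed), power 0.80, 102 evaluable per group, 10 villages per arm, 4 towns. The document gives no intracluster correlation (ICC).

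**Step 1: reproduce the plan's figure.** With pooled variance and mean rate 0.07:

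n = [1.960·√(2·0.07·0.93) + 0.842·√(0.02·0.98 + 0.12·0.88)]² / 0.10² = 101.005, rounded up to 102 per group.

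102/0.8 = 127.5, so 128 recruited per group. Both figures are reproduced. Formula power at 102 is 0.804; exact binomial enumeration gives 0.846.

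**Step 2: control events.** 102 × 0.02 = 2.04 expected. P(none) = 0.98^102 = 12.7%. With 128 per group, 2.56 are expected and P(none) = 7.5%.

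**Step 3: the subject intercept.** The likelihood with a subject term was maximised by quadrature for control/intervention event counts of 2/12, 1/12, 3/10 and 4/14. The maximum lay at subject SD 0 each time. The full model was then fitted with R's glmer to five simulated trials (20 villages of 10, 4 towns). It ran every time, each time with a singular-fit message and subject SD at or near 0. In the one trial with no control event it returned log RR 20.6, SE 483, p = 0.97.

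**Step 4: Wald test of the log risk ratio.** The Poisson standard error is √(1/(102·0.02) + 1/(102·0.12)) = 0.756. The expected z is ln 6 / 0.756 = 1.792/0.756 = 2.37, so formula power is Φ(2.37 − 1.96) = 0.66. With 2 control events, 9 intervention events give z = 1.92 and 10 give z = 2.08, so 10 are needed.

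Exact enumeration, no clustering, 102 per arm (a zero-event arm counts as non-significant for Wald):

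| Test | Power, 2% vs 12% | Type I error, 2% vs 2% |
|---|---|---|
| Chi-squared (planning) | 84.6% | 4.0% |
| Poisson Wald, model variance | 65.1% | 0.06% |
| Poisson Wald, robust variance | 66.3% | 0.06% |
| Poisson score | 82.2% | 4.0% |
| Poisson likelihood ratio | 86.2% | 9.5% |

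Wald needs 143 per group by formula for 80% power, or about 125 to 128 by enumeration. At 128 with no attrition it has 81%.

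**Step 5: Poisson variance at higher prevalence.** Type I error of the Wald test, nominal 5%, 102 per arm, one value per person, no clustering. The 30% and 60% prevalences are assumed:

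| Prevalence | Model variance | Robust variance |
|---|---|---|
| 12% | 3.2% | 4.3% |
| 30% | 1.8% | 4.6% |
| 60% | 0.2% | 5.0% |

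**Step 6: towns and clustering (simulation, ICC assumed).** With town effects, Wald power is 0.60 to 0.62 at ICC 0. It is 0.60, 0.56 and 0.52 at ICC 0.01, 0.03 and 0.05 with the village variance left out of the standard error, which flatters Wald. Regressing 20 village proportions on arm and town leaves 20 − 1 − 1 − 3 = 15 df. That test has about 76 to 77% power at ICC 0 and 61 to 62% at ICC 0.05, with type I error of roughly 2.6 to 3.8% when both rates are 2%.

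**The case against.** Much of the opposing case is fair.

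- **A reader might infer that the model cannot be fitted.** The fits in Step 3 show otherwise. It collapses to the village-intercept model, so the subject term does nothing rather than breaking the analysis.
- **A reader might take the Wald test as the stated primary test.** It is not. It is a reasonable assumption: standard pooling over imputations combines estimates and standard errors, and Wald tests are named for the post hoc comparisons that include six months. It remains an assumption.
- **A reader might blame the Poisson model for the power loss.** At these rates the loss comes from the Wald test. A Poisson score test keeps 82% power at the right level. The likelihood-ratio test keeps power too, but at a type I error of 9.5%.
- **Robust variance, degrees of freedom and a sparse-event rule may be in an analysis plan not shown, or in the cited method papers.** Silence on these is therefore not itself the finding. The stated subject term and the mismatch between planning test and analysis are in the text.
- **Losses that grow with the ICC belong to the sample size.** The village-level test loses power to clustering too. The 65% figure therefore excludes clustering.
- **The secondary models are longitudinal,** so the unclustered one-value figures in Step 5 illustrate direction and scale only. The error is conservative.

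What none of this removes is a redundant term in the primary model, a sizing test that differs from the analysis, and about 2 expected control events.

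**Conclusion.** The point holds in this form. The subject intercept in the six-month model is redundant, whatever the event rates. The Poisson model-based variance is too large for binary outcomes: slightly at 12%, seriously at higher prevalence. The stated 80% power belongs to a chi-squared test. If the primary analysis is a Wald test of the log risk ratio, power at 102 per arm is about 65% without clustering: 14 to 15 points below planning by formula (0.80 to 0.66) and 19 to 20 by exact enumeration (0.85 to 0.65). About one trial in eight would have no finite risk ratio.

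These figures assume a two-sided 5% level, the plan's own 2% and 12%, and 102 evaluable per arm. Imputation does not restore the information lost through attrition, so 102 rather than 128 is the fair basis. The Wald figures depend on the assumed test, the 30% and 60% figures on assumed prevalences, and every clustered figure on an assumed ICC.

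**What to change.** 1. Remove the subject intercept from the six-month model and keep village as the cluster. Leave the subject intercept in the longitudinal models.
2. Name the primary test, choosing one that holds its level with about 2 control events and 20 clusters. One option is a village-level comparison adjusted for town, with a t reference on 15 df or a permutation reference over the admissible allocations. It is somewhat conservative at 2% and should be weighted if village sizes differ. It is an option, not the only acceptable test.
3. Report the risk difference beside the risk ratio. It exists with zero control events and is on the scale of the plan's 10-point minimally important difference. Say what is reported when the risk ratio is not finite, including within imputed sets.
4. For the risk ratio and the repeated binary outcomes, use village-robust standard errors with a small-sample correction, or a logistic mixed model.
5. Restate power for the test named, with the assumed ICC shown. The village-level option also falls short of 80% in Step 6, so this may reopen the sample size.

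Items 1 to 4 cost a few sentences of analysis text and a few lines of R, best settled before outcome data are analysed. The price of the village-level test is a small loss of efficiency when village sizes vary.

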### Randomization and allocation concealment

In this cluster-RCT, recruitment and baseline data collection will be conducted prior to randomization. Cluster randomization, which is necessary for implementation of community-level interventions, mitigates concerns of within-community/village contamination, and improves the feasibility of on-site intervention, will be performed at the community/village level. A total of 20 eligible communities/villages will be randomized using a computer-based random number generator (www.random.org) and assigned to either the intervention group or the control group, with 10 communities/villages in each group. A covariate adaptive procedure will be used to minimize the *P* value from a joint *F* test (1000 iterations) to facilitate covariate balance [34, 35]. Several location level covariates will be considered, including number of village residents, and mean age and sex ratio of residents.

Allocation concealment will be ensured through central randomization [36]. Specifically, an independent statistician will generate a block randomization sequence with randomly permutated block size (4–8) and 1:1 allocation ratio. A sequential list with resulting random numbers will be provided to the study center that recruits villages. Only after participation of a village is confirmed, will the study center reveal labels of the random sequence to the trial team delivering interventions.

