#### Sensitivity analysis

Results for unimputed data will be reported and results of models adjusted for age and gender. Per-protocol analysis including only those who completed the treatment as planned (at least 70 percent of sessions) will also be performed [62]. Considering the likelihood of missing not at random (MNAR) in mHealth studies, we will also use reference group based imputation for establishing the impact of differential attrition on study results assuming that participants who dropped out during the study behaved like control afterwards [63].

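### The village allocation is balanced on number of residents, mean age and sex ratio, but no main model adjusts for these factors, so the main analysis may be conservative by a modest amount

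*Protocol article*

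**What the plan says.** The section Randomization and allocation concealment assigns 20 villages, "with 10 communities/villages in each group", by a covariate adaptive procedure that uses a joint F "test (1000 iterations) to facilitate covariate balance". On the factors it says: "Several location level covariates will be considered, including number of village residents, and mean age and sex ratio of residents". These describe the village and its residents, not the enrolled participants, and the wording leaves the list open. The next paragraph of the section describes a different mechanism: "an independent statistician will generate a block randomization sequence with randomly permutated block size (4–8) and 1:1 allocation ratio".

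The Data analysis section regresses the primary outcome on arm and then says: "In addition, the model will include a random intercept for subject nested in village and a fixed effect for town". Binary secondary outcomes add timepoint and its interaction with arm, "with random intercepts for subject nested in village and fixed effect for town as specified for the primary outcome". Continuous secondary outcomes are "adjusted for the respective outcome at baseline and featuring random intercepts for subject nested in village as well as a fixed effect for town". Under Sensitivity analysis: "Results for unimputed data will be reported and results of models adjusted for age and gender". Age and sex otherwise appear only as modifiers in the exploratory subgroup models. Number of residents appears in no model.

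**The concern.** Forcing an allocation to balance on factors that predict outcome makes the difference between arms vary less over the allocations that could have been chosen. A model that omits those factors still counts the variation they cause between villages as noise. Its standard error then describes unrestricted randomisation, not the design used. Intervals come out too wide, the test rejects too rarely under the null, and part of the precision bought by balancing is not used. With only 20 villages, precision at village level is scarce.

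This is not a detail left open for an analysis plan. The protocol lists the terms of its main models and expressly gives the age and gender adjustment sensitivity status.

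**Working it through.** **1. Allocation factors against model terms.**

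| Factor | Allocation | Primary model | Secondary models | Sensitivity |
|---|---|---|---|---|
| Number of residents | yes | no | no | no |
| Mean age of residents | yes | no | no | participant age |
| Sex ratio of residents | yes | no | no | participant gender |
| Town | not listed | yes | yes | not restated |
| Baseline outcome | not listed | no | continuous only | not restated |

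**2. The plan's own figure.** For 2% against 12%, 80% power, two-sided 5% and no continuity correction:

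n = [1.960·√(2·0.07·0.93) + 0.842·√(0.02·0.98 + 0.12·0.88)]² / 0.10² = (0.707 + 0.298)² / 0.01 ≈ 101.0, rounded up to 102 per group.

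102/0.8 = 127.5, so 128 per group. The stated 204 and 256 reproduce. Expected events among those analysed: 102·0.02 + 102·0.12 = 2.0 + 12.2 ≈ 14. Analysed per village: 204/20 = 10.2.

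**3. How much village-level factors can explain.** The largest share of the variance of a village mean that they can explain is ICC / (ICC + (1 − ICC)/10.2). The ICC is an assumption.

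- ICC 0.02: 0.02/(0.02 + 0.0961) = 17%
- ICC 0.05: 0.05/(0.05 + 0.0931) = 35%
- ICC 0.10: 0.10/(0.10 + 0.0882) = 53%

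**4. Simulation with town effects.** Set-up: 20 villages in 4 towns, 10 analysed per village, best-balanced of 1000 random 10:10 splits on three covariates, village-level t-test with town fixed effects, 2000 runs per cell. R² is the assumed share of between-village variance that the covariates explain. The effect was set at 2.8 standard errors of a simple comparison of arms, so the power column is a reference level and not the trial's power. Percentages, covariates omitted / included:

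| ICC | R² | Type I error | Power | Change in power (points) |
|---|---|---|---|---|
| 0.02 | 0 | 4.6 / 4.7 | 68.5 / 64.1 | −4.4 |
| 0.02 | 0.3 | 5.2 / 5.6 | 66.0 / 64.1 | −1.9 |
| 0.02 | 0.6 | 3.8 / 4.8 | 68.2 / 69.5 | +1.3 |
| 0.05 | 0 | 5.1 / 4.8 | 67.3 / 63.8 | −3.5 |
| 0.05 | 0.3 | 4.1 / 5.1 | 69.1 / 69.7 | +0.6 |
| 0.05 | 0.6 | 3.4 / 5.2 | 68.5 / 73.1 | +4.6 |
| 0.10 | 0 | 4.9 / 5.1 | 68.0 / 64.3 | −3.7 |
| 0.10 | 0.3 | 3.8 / 5.7 | 66.7 / 69.7 | +3.0 |
| 0.10 | 0.6 | 1.9 / 4.8 | 66.2 / 76.8 | +10.6 |

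Simulation error is about √(0.67·0.33/2000) = 1.1 points for each power figure and √(0.05·0.95/2000) = 0.5 points for each type I error.

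The mechanism shows at ICC 0.10, R² 0.6. With covariates omitted, the mean model standard error is 0.214 against an actual standard deviation of 0.183 (0.214/0.183 = 1.17, so 17% too large). With covariates included it is 0.178 against 0.179.

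**5. Binary version at the planned rates** (1500 runs per cell, same village-level test). Omitted / included:

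| Log odds ratio per SD | Type I error | Power, 2% vs 12% |
|---|---|---|
| 0 | 5.0 / 5.5 | 68.6 / 66.2 |
| 0.3 | 4.0 / 4.5 | 67.1 / 67.5 |
| 0.6 | 2.7 / 4.5 | 61.1 / 65.7 |

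**6. Simpler version without town effects** (18 residual degrees of freedom unadjusted, 15 adjusted; two separate runs). Here R² is the share of village-mean variance explained. At 0.1, 0.2 and 0.3, type I error with covariates omitted was 3.7–4.1%, 2.8–3.3% and 2.1–2.4%. Power omitted against included was 79–82 vs 81–84, 82–83 vs 88, and 83 vs 90. Adjusting for non-prognostic factors cost about 1 point (80.6 vs 79.8).

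All of these are linear village-level tests. They approximate the planned Poisson mixed model and are not fits of it.

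**The case against.** The strongest case is that a sparse primary model, with age and gender adjustment stated as a sensitivity analysis, is a reasonable choice for about 14 events. Arm, three town terms and three covariates make seven coefficients, or two events each. The error is on the safe side, its size is unknown, and at R² = 0 adjustment loses power. This stands as a limit on size and as a reason for a fallback. It does not remove the mismatch between allocation and main analysis.

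A reader might infer more than the documents support:

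- **That inference is invalid or type I error inflated.** Under balance it is not; with covariates omitted, type I error stays near 5% or falls below it.
- **That balancing is wasted without adjustment.** In the simpler simulation, unadjusted power was 82–83% at R² = 0.2 to 0.3, against 80% under simple randomisation. Part of the gain is kept.
- **That every model is equally exposed.** Continuous outcomes are adjusted for their baseline value, which may already carry some of what the factors explain. No baseline-adjusted model was simulated.
- **That the loss is large.** Factors explaining half of the village-mean variance would give a standard error 42% too large, but the ceiling in step 3 puts that out of reach unless the ICC is near 0.10.
- **That adjusting for participant age and sex settles it.** The allocation uses values for all residents. Enrolled participants are cohort members with smartphone access, about 13 per village (256/20 = 12.8).
- **That the unadjusted model is confounded because the text speaks of minimising the P value.** Read literally this would favour imbalance, but the same sentence gives balance as its purpose. It is a wording matter for the randomisation section and adds no weight here.

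**Conclusion.** The point holds as a low-cost improvement. The main models omit the factors on which the allocation is to be balanced. If balance is achieved and the factors predict outcome, standard errors are too large and the test is conservative.

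The size rests on assumptions, since the protocol gives neither ICC nor prognostic strength. For ICC 0.02 to 0.10 and weak to moderate prognostic strength (up to about 30% of village-mean variance in step 6), adjustment changes power by roughly 0 to +7 points, with −2 in the weakest prognostic cell of step 4. The +10.6 cell needs three factors to explain 60% of all between-village variance at ICC 0.10. If the factors are not prognostic, adjustment costs about 1 to 4 points.

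The point also depends on the covariate-balancing description being the one carried out. If only the permuted blocks are used, there is no mismatch.

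**What to change.** In the Data analysis section, make the main analysis of the primary and secondary outcomes adjust for the village-level factors actually used in the final allocation, alongside the terms already listed. Close the list before allocation and keep it short. Report the model without these factors as the sensitivity analysis. The participant-level age and gender model can stay as a further sensitivity analysis.

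For the primary outcome, state in advance what happens if the adjusted Poisson mixed model is unstable or does not converge, for example a cluster-summary analysis of village results adjusted for the same factors.

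The cost is a short addition to the text and no new data, because the factors are needed for the allocation anyway. In a village-level analysis with town effects, three factors reduce the residual degrees of freedom from 15 to 12 (20 − 5 and 20 − 8), and a little power is lost if they are not prognostic.

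Separately, the randomisation section must reconcile its covariate-balancing procedure with its permuted-block sequence and correct the wording on the P value. The adjustment should follow whichever procedure is confirmed.
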